### Data collection and statistics

Data will be collected prospectively for all patients including history, physical examination, laboratory data, pathological examination, perioperative clinical information and complications. Data is collected via datasheets on paper and kept securely. All handling cases are managed by subjected identification code or anonymized registration number. In this trial, no loss-to-follow-up patient may be observed within 12 months after surgery, but some patients may develop cancer recurrence. We include patients who die within 12 months of surgery in the analysis. The correspondence table of the anonymizing code and names and the consent form containing the names are kept strictly in separate, lockable, document storage at WMUH. All required parameters will be collected in an SPSS data file (SPSS version 25, IBM statistics, Chicago, IL, USA). All analysis will be done by intention-to-treat in this trial. Statistical analysis of the differences between the TS and FEES groups will be carried out with a chi-square test, Fisher’s exact test, and a Mann-Whitney *U* test. The results of a treatment effect will be estimated with its 95% confidence interval.

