### Study endpoints

The primary endpoint is the incidence of anastomotic stricture within 12 months after esophagectomy. Secondary endpoints include any incidence of anastomotic leakage, aspiration pneumonia, or reflux esophagitis, overall postoperative morbidity within 12 months after surgery, and quality of life (QOL) evaluation according to the Functional Assessment of Cancer Therapy-Esophageal (FACT-E) version 4.0 12 months after surgery [8]. The Comprehensive Complication Index (CCI) is also calculated as the sum of all complications [9].

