### Randomization

After confirmation of the eligibility criteria, intraoperatively, registration is made by telephone to the Central Registry in Wakayama Medical University Hospital (WMUH). Patient randomization in each group is carried out using a series of consecutive numbers and assigned by the WMUH Central Registry. Patients are randomly assigned to either the FEES method group or the TS method group in a 1:1 ratio. Randomization has two stratification factors. The first one is the route of reconstruction (retrosternal or posterior mediastinal route), and the second one is the administration or absence of neoadjuvant chemotherapy. A clinical researcher performs the randomization using computer-generated, random blocks of 4 in the Central Registry of WMUH. Randomization will take place just before cervical anastomosis after feasibility confirmation of both the TS and the FEES method intraoperatively.

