### Surgical procedure

Patients with thoracic esophageal cancer undergo esophagectomy and mediastinal dissection with extensive lymphadenectomy. Patients undergo thoracoscopic esophagectomy in the prone position. Patients with severe pleural adhesions undergo a right thoracotomy via the fourth intercostal space. After the thoracic procedures are completed, the position of the patient is changed to supine and abdominal lymphadenectomy and gastric conduit reconstruction are performed using either an open laparotomy or laparoscopically. Cervical lymphadenectomy is performed in case of three-field lymphadenectomy. A 4-cm-wide gastric conduit is made along the greater curvature of the stomach using the linear-stapling device Echelon 60–3.5 (Ethicon Endo-Surgery, Cincinnati, OH, USA) in both groups. The gastric conduit is pulled upward to the cervical level through the retrosternal or posterior mediastinal route. At the left side of the neck, esophagogastric anastomosis is performed by either the TS or the FEES method. All operations, including anastomosis, are directed by one of two senior esophageal surgeons ([name] or [name]). They have experienced 40 cases or more of the TS method and 20 cases or more of the FEES method at the start of this RCT. They will perform both techniques equally.

The TS method is an end-to-end anastomosis using the 60-mm linear-stapling device Echelon 60–3.5 (Endo-Surgery, Cincinnati, OH, USA). The TS method procedure is composed of three steps: the first step is the firing of the linear stapler at the posterior wall of the cervical esophagus and the gastric conduit after inserting three or four suspension sutures. The second step is the firing of the linear stapler at half of the anterior wall after inserting the suspension sutures. The third step is the firing of the linear stapler at the remnant half of the anterior wall as in the second step. This technique has been described previously [4].

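### The article names two unstratified tests for stricture with no rule for choosing between them, although randomisation is stratified; one stratified test should be named

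*Protocol article*

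**What the plan says.** - **Endpoint** (Study endpoints): "The primary endpoint is the incidence of anastomotic stricture within 12 months after esophagectomy". This is a yes/no outcome for each patient.
- **Allocation** (Randomization): "Randomization has two stratification factors". One is the reconstruction route, retrosternal or posterior mediastinal; "the second one is the administration or absence of neoadjuvant chemotherapy". Allocation is 1:1 using "computer-generated, random blocks of 4". Two binary factors make four strata.
- **Analysis** (Data collection and statistics): "Statistical analysis of the differences between the TS and FEES groups will be carried out with a chi-square test", and the sentence goes on to list Fisher's exact test and the Mann-Whitney test. No test is tied to an endpoint and no selection rule is given. The section adds "The results of a treatment effect will be estimated with its 95% confidence interval" without naming the effect measure. Neither stratification factor is mentioned.
- **Sample size** (Sample size calculation): 20% versus 4%, 80% power, one-sided alpha, 59 per arm, 125 recruited. No test is named there either.

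**The concern.** Two things are left loose in the primary comparison.

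First, chi-square and Fisher are both on the list for a binary outcome with few expected events (59 × 0.20 = 11.8 and 59 × 0.04 = 2.4). Fisher is the more conservative of the two at this size. For borderline tables the primary conclusion therefore depends on which test is quoted, and that could be settled after the data are seen.

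Second, the design balances the arms within four strata, but every listed test treats the data as one unstratified table. If the factors predict stricture, the crude test uses a variance that is too large for the design and gives up some of what stratification was meant to buy.

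**Working it through.** **Inputs.** From the article: TS rate 0.20, FEES rate 0.04, 59 per arm (118 evaluable), power 80%, one-sided test, blocks of 4, two binary strata. Alpha is printed as 0.05% in the sample-size section and as 0.05 in the abstract; 5% is used here, because the literal 0.05% would need 140 to 152 per arm. Stratum-specific stricture rates and stratum sizes are not given, so they are assumed below.

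**Step 1. The planned 59 per arm does not identify the test.**
- One-sided, pooled normal: n = [1.645√(2×0.12×0.88) + 0.842√(0.20×0.80 + 0.04×0.96)]² / 0.16² = 50.
- One-sided Fisher, exact enumeration: 57 needed; 59 gives 82.3% power.
- Two-sided, unpooled normal: (1.960 + 0.842)² × 0.1984 / 0.0256 = 61. Two-sided arcsine: 58.

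The stated 59 is reproduced within two patients by one-sided Fisher and also by two of the two-sided formulas.

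**Step 2. Individual tables at 59 per arm.** Chi-square: z = (a−b)/59 ÷ √[p(1−p)×2/59], with p = (a+b)/118. Fisher: hypergeometric tail.
- For 9 versus 3: p = 12/118 = 0.1017, z = 0.1017/0.0557 = 1.83.
- For 12 versus 4: p = 16/118 = 0.1356, z = 0.1356/0.0630 = 2.15.

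| TS vs FEES strictures | Sides | Chi-square p | Fisher p | Agree at 5%? |
|---|---|---|---|---|
| 9 vs 3 | one | 0.034 | 0.063 | no |
| 10 vs 4 | one | 0.044 | 0.076 | no |
| 12 vs 4 | two | 0.031 | 0.057 | no |
| 9 vs 2 | two | 0.027 | 0.053 | no |
| 12 vs 3 | one | 0.006 | 0.012 | yes |
| 12 vs 2 | one | 0.002 | 0.004 | yes |

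**Step 3. How often the verdicts differ.** Summing binomial probabilities over all tables at 20% versus 4%:
- One-sided: power 88.5% (chi-square) and 82.3% (Fisher); verdicts differ in 6.2% of trials.
- Two-sided: 80.7% and 70.5%; verdicts differ in 10.2%.

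The differences in power equal the disagreement rates (88.5 − 82.3 = 6.2; 80.7 − 70.5 = 10.2), so every disagreement is chi-square rejecting where Fisher does not. With a common rate between 4% and 20%, one-sided type I error is 5.0% to 6.0% for chi-square and 1.1% to 3.2% for Fisher.

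**Step 4. Effect of ignoring the strata.** The crude variance splits as p(1−p) = mean of p_j(1−p_j) + variance of p_j, and balance within strata removes the last term from the true variance. Assume stratum rates 5/12/25/38% in four equal strata (mean 20%):
- Variance of p_j = (0.15² + 0.08² + 0.05² + 0.18²)/4 = 0.016, out of 0.16.
- True to assumed standard error = √(0.144/0.16) = 0.949.
- One-sided size of the crude test = P(Z > 1.645/0.949) = P(Z > 1.73), about 4.2%.

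Simulation with these rates (8,000 trials, blocks of 4) gave 3.8% crude and 4.8% for Cochran-Mantel-Haenszel (CMH), with power 89.3% versus 90.4% one-sided and 81.5% versus 83.0% two-sided. A separate simulation (118 patients, 20,000 trials per scenario, common odds ratio (0.04/0.96)/(0.20/0.80) = 1/6) gave:

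| Assumed TS rates by stratum | Type I, one-sided: crude / CMH | Power, one-sided: crude / CMH | Power, two-sided: crude / CMH |
|---|---|---|---|
| 20% in all | 5.1% / 5.1% | 88.4% / 88.5% | 80.9% / 80.5% |
| 12/16/22/30% | 4.6% / 4.9% | 87.7% / 88.1% | 79.7% / 79.8% |
| 5/10/25/40% | 4.2% / 5.1% | 86.4% / 87.8% | 77.5% / 79.3% |

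Simulation error is about √(0.05×0.95/20000) = 0.15 points for type I error and √(0.88×0.12/20000) = 0.23 points for power, so gaps of 0.1 mean nothing.

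**The case against.** The best defence is that this is a condensed article. Its sentence on tests covers all endpoints, since Mann-Whitney cannot be meant for a yes/no outcome, and the approved full protocol, which is not shown, may name one test or an adjusted analysis. That is possible. But the tests the article does name are all unstratified and two of them fit the primary endpoint, so the stated method can be improved whatever else exists. If the full document already names one test, the remaining task is to align the published text.

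A second defence is the common convention of using Fisher only when an expected count is below 5. The article does not state it. With equal arms it applies only at nine or fewer events in total, about 8% of trials under the design rates, and it would select chi-square for every table in Step 2. It would settle the choice if written down. Without it, 9.2 of the 10.2 points of two-sided disagreement fall at ten or more events.

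Three stronger readings are tempting, and none is supported.
- *The tests usually conflict.* They do so in 6 to 10% of trials and not at the expected counts. The 12 versus 4 table conflicts only two-sided, whereas the sample size is one-sided.
- *Ignoring the strata endangers a positive result.* The effect runs the other way: the crude test is conservative. Nor does quoting the more favourable of the two tests push type I error above that of chi-square, because Fisher never rejects alone.
- *Surgeon should be adjusted for.* The article does not say surgeon is an analysis variable. It says of the two senior surgeons: "They will perform both techniques equally". Nothing in the text shows confounding by surgeon.

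**Conclusion.** The point holds at moderate weight. The open choice of test is the weightier half: it changes the verdict in about 6% of trials one-sided and 10% two-sided at the design rates, and the 80% power claim depends on it (two-sided Fisher would have 70.5%).

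The missing stratification is a small loss of efficiency and not an error-rate hazard: about 4% instead of 5% one-sided type I error if the factors are strongly prognostic, and about 0 to 2 points of power. If they are not prognostic, stratifying costs at most about half a point (80.9% to 80.5% two-sided).

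The disagreement figures rest only on the article's rates and sample size, with alpha read as 5%. The stratification figures rest on assumed stratum rates and four equal strata.

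**What to change.** In Data collection and statistics, name one primary analysis for stricture:
- the Cochran-Mantel-Haenszel test stratified by reconstruction route and neoadjuvant chemotherapy, at the sidedness used for the sample size, with that sidedness and the alpha level written out. State whether a continuity correction is used; the figures above are without one;
- a Mantel-Haenszel risk difference over the same four strata with its confidence interval, as the effect estimate;
- crude Fisher's exact test as a sensitivity analysis only.

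No surgeon stratum is needed. The cost is a few lines of protocol or analysis-plan wording; sample size, randomisation and data collection stay as they are, since both stratification factors are already known at randomisation. The article reports 34 patients enrolled with recruitment continuing. The change should be dated and made before stricture results are seen by arm.

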### Ethics

The study is conducted in accordance with the Declaration of Helsinki. WMUH Institutional Review Board approved the final version of the protocol (version 1.0) prior to the start of the study (approval number: 1943). This study was registered on the University Hospital Medical Information Network Clinical Trials Registry. (UMIN000025632) (Additional file 1).

### Monitoring

In-house monitoring will be performed every year by a third party to monitor the progress and review the safety and quality of the study.

### Surgical procedure

Patients with thoracic esophageal cancer undergo esophagectomy and mediastinal dissection with extensive lymphadenectomy. Patients undergo thoracoscopic esophagectomy in the prone position. Patients with severe pleural adhesions undergo a right thoracotomy via the fourth intercostal space. After the thoracic procedures are completed, the position of the patient is changed to supine and abdominal lymphadenectomy and gastric conduit reconstruction are performed using either an open laparotomy or laparoscopically. Cervical lymphadenectomy is performed in case of three-field lymphadenectomy. A 4-cm-wide gastric conduit is made along the greater curvature of the stomach using the linear-stapling device Echelon 60–3.5 (Ethicon Endo-Surgery, Cincinnati, OH, USA) in both groups. The gastric conduit is pulled upward to the cervical level through the retrosternal or posterior mediastinal route. At the left side of the neck, esophagogastric anastomosis is performed by either the TS or the FEES method. All operations, including anastomosis, are directed by one of two senior esophageal surgeons ([name] or [name]). They have experienced 40 cases or more of the TS method and 20 cases or more of the FEES method at the start of this RCT. They will perform both techniques equally.

The TS method is an end-to-end anastomosis using the 60-mm linear-stapling device Echelon 60–3.5 (Endo-Surgery, Cincinnati, OH, USA). The TS method procedure is composed of three steps: the first step is the firing of the linear stapler at the posterior wall of the cervical esophagus and the gastric conduit after inserting three or four suspension sutures. The second step is the firing of the linear stapler at half of the anterior wall after inserting the suspension sutures. The third step is the firing of the linear stapler at the remnant half of the anterior wall as in the second step. This technique has been described previously [4].

The FEES method is a side-to-side anastomosis using the linear-stapling devices Echelon 45–3.5 and Echelon 60–3.5 (Ethicon Endo-Surgery Cincinnati, OH, USA). The posterior wall of the esophageal stump and gastric conduit are placed side by side. Two suspension sutures are placed to secure anastomosis through all layers of the posterior wall of the remnant esophagus and the gastric conduit, then the two forks of the linear stapler Echelon 45–3.5 (Endo-Surgery, Cincinnati, OH, USA) are placed and then fired. After three or four suspension sutures have been placed in the anterior wall of the esophagus and the gastric conduit, the second firing of the stapler is performed for the anterior wall using the Echelon 60–3.5 (Endo-Surgery, Cincinnati, OH, USA) (Fig. 1).

Patients undergo cervical computed tomography (CT) after swallowing water-soluble contrast medium 8 days after surgery. Normal oral intake is allowed after integrity of the anastomosis is confirmed using diagnostic modalities. After discharge, patients are examined at 3, 6, and 12 months after surgery.

### Definition of postoperative complications

Patients routinely undergo postoperative gastrointestinal endoscopy at 12 months or if complaints of symptoms such as dysphagia arise. In this study, anastomotic stricture is a condition that requires balloon dilation of the stenotic anastomosis, with endoscopic proof of a stenosis through which a 9-mm endoscope cannot be passed by esophagogastric anastomosis. Anastomotic leakage is defined as the presence of extraluminal contrast by postoperative CT after swallowing contrast medium, endoscopic visualization of dehiscence or fistula, or flow of saliva or pus through the cervical wound. If pus from the cervical wound with uncertain anastomotic leakage is found, patients undergo a contrast-medium swallow study and a CT study after open drainage of the cervical wound to confirm the existence of anastomotic leakage. Reflux esophagitis is defined as greater than grade A according to the Los Angeles Classification System. Other overall postoperative morbidities are redefined as greater than grade II by the Clavien-Dindo classification [10].

### Follow-up

Follow-up appointments for all patients will take place at 3, 6, and 12 months following surgery at WMUH. All patients are followed up for 5 years or until death. The enrollment of this trial will be complete by December 2019 and the 12-month follow-up will continue until December 2020 (Fig. 3). The 5-year follow-up of the final participant will be complete by December 2024.

**Fig. 3 Fig3:**
[figure not shown]
Timeline

## Discussion

Our previous study comparing the TS method and the CS method showed no significant difference in anastomotic stricture (TS group 18%; CS group 17%; *P* = 0.0935), anastomotic leakage (TS group 2%; CS group 11%; *P* = 0.073), aspiration pneumonia (TS group 6%; CS group 13%; *P* = 0.239), reflux esophagitis (TS group 12%; CS group 13%; *P* = 0.878), or overall morbidity (TS group 69%; CS group 70%; *P* = 0.999) [4].

To investigate the optimal anastomotic method in cervical esophagogastric anastomosis after esophagectomy, we proceed with a further prospective RCT. The reported incidence of anastomotic stricture for the FEES method was lower than for the TS method in cervical esophagogastric anastomosis. This is the first RCT to provide evidence of whether the FEES method reduces the frequency of anastomotic stricture in cervical esophagogastric anastomosis after esophagectomy for esophageal cancer.

The FEES method produces a larger anastomotic area, which is thought to reduce anastomotic stricture. The FEES method is popular in colonic surgery today, but in esophageal surgery the FEES method has not yet become popular and only a few surgeons use this method in esophageal surgery. The FEES method needs only two lots of stapling for esophagogastric anastomosis and can reduce operation time.

## Trial status

The WMUH Institutional Review Board approved the final version of the protocol prior to the start of the study (approval number: 1943). The first patient was recruited on 30 January 2017. Currently, 34 patients have been enrolled in this trial and patient recruitment continues. The projected completion date for this trial is December 2019.

## Abbreviations

CS: Circular stapling
CT: Computed tomography
FEEA: Functional end-to-end anastomosis
FEES: Functional end-to-end stapling
RCT: Randomized controlled trial
TS: Triangulating stapling
WMUH: Wakayama Medical University Hospital
